### Additional analyses

#### Self-control networks

Dynamic relations between self-control variables will be analyzed and visualized with the network approach [24] for the baseline (week 1) and post-intervention period (week 6) as well as for other timeframes. For computing estimates of the multilevel VAR models, the R package mlVAR will be used [61]. Networks will be constructed out of selected ambulatorily assessed variables (e.g., self-control depletion, mindfulness, negative affect, negative event, conflict and desire strength). First, multilevel VAR models are modelled for each network variable – every single network variable is regressed to a lagged version of itself and all other independent lagged variables (values that were measured at a previous time point). These multilevel VAR models contain fixed and random effects where the fixed effects are the average population effects of the lagged variables on the dependent variable (group level) and the random effects the participant’s deviations of the average population effect (individual level). Then, the fixed-effects coefficients of all modelled multilevel VAR models are used to visualize directed relationships between all network variables. The self-control population network containing average connection strength between variables at group level will be visualized with the qgraph R package [62]. In accordance with Bringmann et al. [24], the False Discovery Rate [63] will be controlled at 5% in order to control for multiple testing. An exemplary network is presented in Fig. 2 showing time-to-time relations (edges) between network variables (nodes). For a more detailed description, see Bringmann et al. [24]. This procedure will also be applied to construct population networks for the control as well as for the mindfulness condition in specific health domains like alcohol consumption, emotion regulation and eating behavior.

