#### Secondary objective

A novel network approach [24] will be used to model the interplay of momentary self-control with internal and external factors, such as affect, desire strength and positive or negative events, over time. These time-to-time relationships will be analyzed at individual and group level by using multilevel VAR models. Afterwards, different network parameters will be computed exploring overall and local network structure (see “Statistical analysis”). In doing this, (1) underlying processes of self-control enactment become visible, (2) predictors of self-control from a range of different domains will be identified and (3) it is possible to examine mediating processes that convey the effect of mindfulness training on momentary mindfulness, and ultimately on self-control in daily life.

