#### Ambulatory Assessment protocol

A day after the first laboratory session, the Ambulatory Assessment begins (day 1 till day 40). Each day, signals are randomly distributed six times a day via smartphones throughout a defined timeframe of 10 h. Signals can occur between 10 a.m. and 8 p.m. This time span is divided into blocks of 2 h [56], defining for each block that two consecutive signals could be at least 45 min apart. Throughout a timeframe of 5 min after a signal, participants can start, reject or postpone their answer for 15 min. Participants are asked to complete short questionnaires which assess experiences at the present moment or within the last 30 min [7].

Moto E (second generation) smartphones with the latest Android Lollipop version 5.1 are handed to participants in case they do not own an Android-based smartphone. Ambulatory Assessment is run via the application movisensXS, version 0.8.4203 (movisens GmbH, Karlsruhe, Germany), which has to be downloaded and installed either on the personal or the received smartphone. This app schedules the beeping signals, presents the questionnaires on the smartphone and saves collected data by uploading it to a secured server.

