### Primary and secondary outcome analysis

First, the effect of mindfulness training on momentary mindfulness and self-control will be explored. Since Ambulatory Assessment data have a hierarchical structure, where several observations are nested within each day and days are nested within individuals, we use three-level multivariate mixed models including random effects for each level-1 variable (daily observations) allowing for within-day (level 2) and within-person (level 3) variations. In this way, time-varying momentary mindfulness and self-control on level 1 (daily observations) will be predicted by day (level 2) and group (level 3), controlling for age, gender, social desirability and other personality traits at level 3. Significant main effects of the variables day and group would indicate group differences and a change of momentary mindfulness and self-control across time. Furthermore, significant two-way interactions between the continuous variable day (level 2) and the categorical variable group (level 3) would indicate an effect of mindfulness training on momentary mindfulness and self-control relative to the control condition in everyday life.

The secondary outcomes habitual mindfulness and self-control are examined using mixed models. Two-way interactions between laboratory meetings (seven meetings) and group (mindfulness versus control) predicting habitual mindfulness and self-control would indicate differences between groups from one meeting to another. Further additional momentary and habitual measures will be examined in a similar manner.

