#### Effects of mindfulness on the self-control network

In order to investigate the effect of mindfulness on the interconnections of the self-control network, a treatment variable (mindfulness versus control) and a time period variable (pre versus post intervention) will be added to the multilevel VAR models of the population network [24]. Differences between mindfulness and control conditions can be examined by looking at single links between two specific variables within the network [24]. If there is a change across time at a specific link between a lagged independent and a dependent variable that differs between conditions, there should be a significant three-way interaction between the variables treatment, time period and the independent lagged variable on the dependent variable.

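### The network equations carry no time-of-day or diary-day term, so variables that merely share a trend can be drawn as directed links to self-control

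*Protocol article*

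**What the plan says.** Under Self-control networks, the protocol article gives the right-hand side of each equation: "every single network variable is regressed to a lagged version of itself and all other independent lagged variables". The fixed effects are described as the average effects of these lagged variables, with random person deviations around them. Then "the fixed-effects coefficients of all modelled multilevel VAR models are used to visualize directed relationships between all network variables". Networks are fitted "for the baseline (week 1) and post-intervention period (week 6) as well as for other timeframes", and the Fig. 2 caption gives the baseline window as days 1 to 6. The false discovery rate is held at 5%.

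The data come from a diary in which "Each day, signals are randomly distributed six times a day via smartphones throughout a defined timeframe of 10 h". Under Secondary objective, one stated gain is that "predictors of self-control from a range of different domains will be identified". Density and centrality are computed from the same coefficients (Network structure).

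The only non-lagged terms named for these models stand under Effects of mindfulness on the self-control network, where "a treatment variable (mindfulness versus control) and a time period variable (pre versus post intervention) will be added". The primary mixed model, by contrast, does have diary day as a predictor. The article does not say whether the last prompt of one day is paired with the first prompt of the next.

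**The concern.** If two variables both rise over the day, or both drift over the days of the window, the earlier value of one predicts the later value of the other even when neither influences the other. A model with lagged variables only has nowhere else to put the common trend, so it loads it onto the cross-lagged coefficients. These are then non-zero in the fitted model. The false discovery rate procedure treats them as true signals and keeps them.

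Pre/post period and treatment do not absorb a trend inside a day or inside a week. The plan itself allows for change across days: its primary analysis tests for it in momentary mindfulness and self-control, and both constructs are represented among the example network nodes.

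At stake are the population, arm-specific and domain-specific networks, their density and centrality, and the list of predictors of self-control drawn from them.

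**Working it through.** **Inputs from the protocol article.** Six example nodes (Self-control networks, Fig. 2); six prompts a day (Ambulatory Assessment protocol); days 1 to 6 (Fig. 2); 120 people, 60 per arm (Sample size); 5% false discovery rate.

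**Assumptions, because the article gives no values.** Four of the six nodes share a linear trend that takes a share *s* of within-person variance; *s* = 2, 5 or 10%; autoregression φ = 0.3; no true cross-links; full response. Four nodes give 4 × 3 = 12 affected links.

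**The plan's own figure.** There is none for the networks. The 120 itself reproduces: 4(1.960 + 1.645)²/0.33² = 477.3, times (1 + 239 × 0.25)/240 = 0.253, gives about 121. The point does not depend on it.

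**Step 1: expected false coefficient.** Write each of *K* standardised nodes as √s·T + √(1−s)·e, with a common trend T and independent noise e of autoregression φ. Let ρ be the lag-1 correlation of T over the pairs used. Solving the normal equations gives

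b = (ρ − φ)s / (1 + (K − 1)s).

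The bias is positive when the trend persists from prompt to prompt more strongly than the noise does.

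**Step 2: trend across days.** Within a day T is constant, so ρ = 1. With K = 4:
- s = 2%: 0.7 × 0.02/1.06 = 0.013
- s = 5%: 0.7 × 0.05/1.15 = 0.030
- s = 10%: 0.7 × 0.10/1.30 = 0.054

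Same-day pairs number 120 × 6 × 5 = 3,600, so the standard error is about √(0.91/3600) = 0.016. The ratios are about 0.8, 1.9 and 3.4, which means significance at 5% in roughly 13, 48 and 92% of tests.

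**Step 3: linear drift within the day, same-day pairs only.** ρ = 1 again, but the predictor uses prompts 1 to 5, where the drift has variance 2.0 against 2.917 over all six. At s = 10% the effective share is 0.0686/0.9686 = 0.071, so b = 0.7 × 0.071/1.21 = 0.041. The ratio to the standard error is about 2.6, or roughly 73%.

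**Step 4: the same drift with overnight pairs kept.** With centred prompt values −2.5 to 2.5, the five same-day products sum to 8.75 and the evening-to-morning product is −6.25. Over six days and five nights: (6 × 8.75 − 5 × 6.25)/35 = 0.607, and ρ = 0.607/2.917 = 0.21. At s = 10%, b = (0.21 − 0.3) × 0.10/1.30 = −0.007. The overnight reset cancels the drift.

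**Step 5: simulation.** Six nodes, 120 people, days 1 to 6, full response, person-centred lag-1 regressions with person-clustered errors, Benjamini–Hochberg at 5%. The table gives the percentage of affected null links with p < .05.

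| Shared trend | Pairs | s = 2% | 5% | 10% |
|---|---|---|---|---|
| Linear across days | either | 14–17 | 55 | 96 |
| Linear within day | same-day | 9 | 32 | 79 |
| Linear within day | overnight kept | 5–8 | 5–8 | 5–8 |

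At 10%, about 12 false links survive the false discovery rate step for the day trend, and 8 to 9 for the within-day drift with same-day pairs. A midday peak with same-day pairs gives 7% at s = 10%.

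**Step 6: sensitivity.** At 80% response, the within-day drift with same-day pairs at 10% leaves about 5 to 6 surviving false links. With 60 people and full response, about half of the affected links are significant and about 4 survive. Two further runs let all six nodes share the rhythm, at 80% response with overnight pairs kept. There a midday peak at 10% gives 14% significant in one week. Over 40 days 46% survive the false discovery rate step.

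**Step 7: with prompt number and diary day in the model,** the rates return to about 4–6% and 0.2–0.4 surviving links.

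Pooled regression stands in for the mlVAR package throughout.

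**The case against.** The strongest reply is that the result depends on pairing. The article says only that lagged values come from a previous time point, and a literal reading keeps overnight pairs. A linear daily rhythm then does almost no harm in a one-week window. This stands, and it rules out the claim that a shared daily rhythm will in general produce false links. It does not help against a trend across days, which inflates under either pairing.

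Second, the size, shape and shared direction of any trend are assumed. That also stands: at 2% of variance the harm is small, and a midday peak does little in one week. The one-week windows limit long drifts but not a trend inside the week, and the article allows other, unspecified timeframes.

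Third, this is a condensed article that points to a cited method paper for detail. That would answer a missing regressor list, but here the list is given and only treatment and period are ever added to it. A fuller document may still contain the terms.

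Fourth, the article calls the network work exploratory. That is correct and limits the consequence. It is nonetheless one of the study's two declared aims, and its edges are to be read as predictors.

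A reader might go on to infer that the trial's treatment comparisons are compromised. The document does not support that. The primary mixed models include day and do not use these equations, and a trend common to both arms mostly cancels in the treatment × period × lagged-variable test.

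**Conclusion.** The point holds in a conditional form. As written, the network equations contain lagged variables only, and variables that share a trend over the day or over the window can be drawn as directed links that false discovery rate control does not remove.

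The firmest part is the trend across days: about 15/55/96% of affected null links are significant at 2/5/10% of within-person variance, whatever the overnight pairing. The within-day part (about 9/32/79%) applies only if pairs are restricted to the same day. These figures assume a linear trend shared by four of six nodes, autoregression 0.3, 120 people and full response. The document neither confirms nor excludes such trends, so it cannot be said that false links will occur, only that the model has no protection against them.

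The damage is limited to the exploratory population and arm-specific networks, with their density and centrality. It is worth correcting because those networks carry the secondary objective and the correction is small.

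**What to change.** In each VAR equation, for every window and arm, add prompt number (1 to 6, as a factor) or clock time, plus diary day, as fixed covariates. Both are needed, since a diary-day term does not remove a daily rhythm and a prompt term does not remove a trend across days. State whether overnight pairs are excluded. Compute edges, density and centrality from the lagged coefficients of the adjusted model, and show the unadjusted network as a sensitivity analysis.

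The cost is a sentence or two in the analysis section and a few degrees of freedom. There is one real downside: genuine influence that coincides with the clock or the day trend, such as depletion building up over the day, is also removed from the adjusted network. Showing both versions lets the reader see which links depend on the adjustment.

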**Fig. 2 Fig2:**
[figure not shown]
Time-to-time dynamics between several variables at baseline (day 1 till day 6). Variables: SCD = self-control depletion; M = mindfulness; NA = negative affect; NE = negative event; C = conflict; D = desire strength. Solid arrows represent positive relations and dashed arrows represent negative relations. The thicker the line the higher is the fixed-effect coefficient. In this case, only coefficients reaching significance are presented (*p* < .05)

#### Individual self-control networks

By using a subject’s individual random effects with the fixed-effect coefficients of the multilevel VAR models, networks can be visualized that show only temporal dynamics of a specific subject. In this way, individual self-control networks can be visualized [24].

#### Effects of mindfulness on the self-control network

In order to investigate the effect of mindfulness on the interconnections of the self-control network, a treatment variable (mindfulness versus control) and a time period variable (pre versus post intervention) will be added to the multilevel VAR models of the population network [24]. Differences between mindfulness and control conditions can be examined by looking at single links between two specific variables within the network [24]. If there is a change across time at a specific link between a lagged independent and a dependent variable that differs between conditions, there should be a significant three-way interaction between the variables treatment, time period and the independent lagged variable on the dependent variable.

#### Network structure

To assess local and overall network structures and their changes, several network parameters, such as network density (overall connectivity) and centrality (In-strength, Out-strength, Closeness and Betweenness), will be analyzed for individual and population networks [64]. Density indicates the overall connection strength between all nodes (variables) and is calculated by averaging over the absolute values of all regression coefficients. High density represents strong interconnections between the network variables which means they have high impact on each other from one time point to the next. Different centrality indices [65] will be computed for all network variables to explore the importance within the network of each of them. Those indices indicate how much information a specific node exchanges with other nodes or how close it lies to the others (for a detailed description see Bringmann et al. [24, 64]).

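### Network density averages self-effects together with cross-links but is read as the variables' impact on each other

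*Protocol article*

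**What the plan says.** All references are to the protocol article.

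- **Self-control networks** sets out the model: "every single network variable is regressed to a lagged version of itself and all other independent lagged variables". Example nodes are "self-control depletion, mindfulness, negative affect, negative event, conflict and desire strength", which makes six. Networks are to be built for week 1, week 6 and other timeframes, and the False Discovery Rate is controlled at 5%.
- **Network structure** gives the scoring rule: density "is calculated by averaging over the absolute values of all regression coefficients". It then gives the meaning: "High density represents strong interconnections between the network variables which means they have high impact on each other from one time point to the next". Density and the centrality indices "will be analyzed for individual and population networks", in order to assess network structure and how it changes.
- The False Discovery Rate control, and the display of significant edges only in Fig. 2, are not said to apply to the density calculation.

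**The concern.** The rule and its stated meaning do not match. The rule averages every coefficient, and every equation includes the variable's own lag. The meaning concerns only what one variable does to another. A variable's effect on itself is inertia, not interconnection.

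At stake is how a change in density would be described. Suppose training shortened the carry-over of negative affect or depletion from one prompt to the next and left every link between variables as it was. Density would fall, and the stated reading would be that the variables influence each other less. That is a different conclusion about mechanism, and mechanism is what the secondary objective is about.

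A second, smaller issue is that a mean of absolute estimates is above zero even when every true coefficient is zero, by an amount that depends on how much data enters. Raw densities from windows of different length or completeness are therefore not on the same footing.

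**Working it through.** The article states no density value, so there is no figure to reproduce.

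**Count.** With p = 6 nodes there are p × p = 36 lagged coefficients: p = 6 self-effects (16.7%) and p(p − 1) = 30 cross-lags (83.3%).

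**Share of the score.** Let s be the mean absolute self-effect and c the mean absolute cross-lag. Then density = (6s + 30c)/36, and the self-effect share is 6s/(6s + 30c) = s/(s + 5c). The article gives neither s nor c, so the values below are assumptions.

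| s | c | density | self-effect share |
|---|---|---|---|
| .30 | .04 | (1.8 + 1.2)/36 = .083 | 1.8/3.0 = 60% |
| .30 | .05 | (1.8 + 1.5)/36 = .092 | 1.8/3.3 = 54.5% |
| .30 | .10 | (1.8 + 3.0)/36 = .133 | 1.8/4.8 = 37.5% |

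Self-effects form the majority only when s exceeds 5c.

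**Self-effects change, links do not.** Let s fall from .30 to .20.

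- At c = .04, density goes from .083 to (1.2 + 1.2)/36 = .067, a fall of 20%.
- At c = .10, it goes from .133 to (1.2 + 3.0)/36 = .117, a fall of 12.5%.

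The mean over the 30 cross-lags is unchanged in both cases.

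**Simulation with no true links.** Six nodes, 60 participants, 6 days of 6 prompts, within-day lags, person-mean centring, full compliance, identical persons, independent unit-variance errors, 40 replicates. A pooled regression stands in for the population network.

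| true self-effect | density as written | cross-lags only |
|---|---|---|
| 0 | .021 | .019 |
| .2 | .044 | .020 |
| .3 | .060 | .019 |
| .4 | .076 | .019 |
| .5 | .090 | .017 |

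Density as written rises about fourfold with no link present. The cross-lag mean stays nearly flat.

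**Links still count.** With s = .30, raising the true cross-lags from 0 to .05 to .10 moves density as written from .060 to .084 to .123.

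**Noise floor.** With all true coefficients zero, population density is .032 for 3 days, .025 for 4, .021 for 6 and .0075 for 40. For individual networks over 6 days it is .029 after shrinkage towards the group mean, and .166 from unshrunken person-by-person regressions. Dropping the self-effects does not remove this floor: the cross-lag mean is .019, .029 and .167 for the population, shrunken individual and unshrunken individual networks over 6 days.

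**The case against.** The case for leaving the rule alone has several parts.

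- **The index still responds to links.** A reader might infer that density does not measure interconnection at all. The definition does not support that: 30 of the 36 coefficients are cross-lags, and the score rises with them. It is a mixed measure, not an unrelated one. This stands.
- **The share is assumed.** A reader might also infer that density mostly scores inertia. That needs coefficients which the article does not give. At cross-lags of .10 the share is below one half. This stands, so only the range can be quoted.
- **Noise is a small matter here.** The floor is about .02 for population networks and .03 for shrunken individual ones, and it largely cancels when arms and periods contribute equal data. It is tempting to say that falling diary compliance would push density up materially. With true links of .04, however, going from 85% to 65% answered prompts moves density only from .083 to .085 in simulation. With links of .10 the cross-lag mean hardly moves (.102 to .100). The raffle also rewards completing more than 80% of questionnaires. This stands for realistic response rates.
- **Convention.** The section cites published sources for these parameters, which are not at hand, and a changed definition costs comparability. This is met by reporting both values.
- **Low stakes.** The Background calls the network analyses exploratory. The effect of training on single links is tested by a three-way interaction (Effects of mindfulness on the self-control network) that does not use density. The article does not say that raw density differences will be tested, and a reference distribution may be left to an analysis plan. Its absence is therefore not counted as a fault.

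None of this removes the mismatch between what the rule averages and what the same paragraph says it means.

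**Conclusion.** The concern holds as a mismatch between a stated formula and its stated interpretation. By the article's own model description, density includes 6 self-effects among 36 coefficients in the six-node example, yet it is read as impact between variables. The count follows from the text alone. The size rests on assumption: with self-effects of .30 and cross-lags of .04 to .10, self-effects supply 60% to about 38% of the score, and a drop in self-effects to .20 alone lowers density by 20% to 12.5%. The simulated figures further assume within-day lags and a pooled regression in place of the full multilevel fit.

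The point is minor. Density serves an exploratory part of the secondary objective, and no primary or secondary outcome depends on it. It is worth correcting because the rule as written can lead to a wrong statement about mechanism and the remedy is cheap.

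**What to change.** In Network structure, define density as the mean absolute value of the cross-lagged coefficients only, p(p − 1) = 30 for six variables. Report the mean absolute autoregressive coefficient separately as inertia. List the all-coefficient value beside them for comparison with work that uses that definition.

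If densities are compared between arms, periods or windows that differ in the number of usable lag pairs, judge the difference against a parametric bootstrap that simulates no change at the observed lag pairs. Shuffling condition labels is not enough by itself. It breaks any link between arm and compliance: with identical dynamics, no cross-links and a deliberately extreme 85% versus 40% response, it rejected in nearly every one of 100 simulated trials at the .05 level. It also cannot judge a week 1 versus week 6 change.

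The cost is a sentence or two of text, a few lines of R on the mlVAR output and some computing time for the bootstrap. No new data are needed. The headline density will usually be numerically smaller than all-coefficient values, which is why both should be shown.
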